### Biochemical assessment

At the 12-month visit, 6 mL of blood will be drawn from each child by venipuncture, preferably from the cubital vein. Each aliquot will be divided into 3 different tubes for analysis, containing 3 mL of blood each: namely: blacktop with no gel, for ferritin; and lavender top, containing the chelating agent ethylenediaminetetraacetic acid (EDTA), for complete blood count.

After blood collection, a pressure dressing will be placed at the puncture site and children will be instructed not to bear weight or apply force with the punctured arm for at least an hour [39].

If the child has an evident inflammatory or infectious condition at the time of collection, the procedure will be postponed to 14 days after remission of symptoms, in order to avoid possible momentary changes in laboratory parameters due to the disease.

#### Adverse events

We intend to monitor any adverse event caused by the trial participation. Presence of choking incidents will be identified in the questionnaires along with possible growth faltering, identified during the 9- and 12-month anthropometric measurement sessions. We will pay special attention to monitor multiple occurrences of adverse events in a specific participant as well as a high prevalence of any adverse event in multiple participants.

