Considering several questions raised by parents and healthcare professionals regarding the BLW method, such as possible risks of choking and inadequate supply of iron and calories, a group of New Zealand professionals created a modified version of this approach, which they named Baby-Led Introduction to SolidS (BLISS). The BLISS recommendations are the same as those of the BLW method, with some additional advice, including offer food shaped in large pieces, which the infant can hold by himself; guarantee one source of iron-rich food at each meal; offer a high-calorie food at each meal; offer prepared foods in a texture that reduces the risk of choking, and avoid foods listed as high risk of aspiration; always try the food before offering it to the infant, to check it does not become solid in the oral cavity; avoid round or coin-shaped foods; and ensure that the infant is seated, erect, and under supervision of an adult. A study compared the BLW and BLISS approaches, where BLISS participants received two intervention visits, resources, and on-call support, while BLW participants received no intervention. Findings showed that the BLISS intervention allowed to increase the offerings and variety of iron-containing foods and to reduce the offering of high-choking-risk foods [14].

Although the Brazilian guideline for CF has been reviewed and republished recently, the conventional method, Parent-Led Weaning (PLW), is still advised, and there are no recommendations for a baby-guided approach in Brazil [13]. Likewise, the current World Health Organization (WHO) guidance proposes pureed foods in the early stages of CF, with consistency progressing gradually along the first year of life [15]. Within this context, the present study intends to contribute to the following outcomes:

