### Randomization

After signing the consent form, participants will be sequentially numbered and have their names entered into a randomization list of three blocks and equal numbers, previously computer-generated (http://www.randomization.com) by blinded research staff.

Only at the time of the first intervention will mothers be aware of their group allocation. Assessment data will be collected by a different researcher from the one responsible for the intervention, blinded to the allocation group, in a different room.

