Second, a home visit at 9 months of age will serve to measure anthropometric parameters of the mother and child. At this time, questionnaires will also be administered and any extra individualized advice or support for the CF process will be provided, always appropriate for the approach to which each mother-child pair was allocated. The visits will be led by two blinded researchers; to avoid unblinding, one will obtain anthropometric measurements before the other applies the questionnaire, as some answers given might reveal the allocation group. The visit will end with a thank-you card, to motivate family engagement with the study.

Finally, the last intervention will be conducted at the HCPA Clinical Research Center (CRC). Blood samples will be drawn for measurement of plasma ferritin, C-reactive protein (CRP), and a complete blood count, as well as saliva for genetic tests. Anthropometric measurements will be repeated, an intraoral examination will be performed, and the end-of-study questionnaires will be administered, as well as a flavor preference test. Mothers will then receive a booklet with advice on healthy nutrition and oral habits, such as nutritional assessment, oral evaluation, and oral hygiene guidance; blood test results; and nutritional guidelines for the child’s further years to come, encouraging them to continue to pay attention to healthy eating.

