### Choking

At the 9-month and 12-month visits, choking and gagging will be assessed by specific questions regarding frequency, a description of which food or drink and consistency was involved, how many times it occurred and maneuvers used to resolve the episode. Researchers will be trained to make sure they are able to distinguish a gagging event from a choking event while applying the questionnaire. We also hope the video examples shown to participants during the first intervention will help them distinguish between the two when reporting events to the researchers.

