### Quality control

Each mother-child pair will receive a specific identification code number, corresponding to the questionnaires and examinations performed, to maintain the anonymity of the participants. To ensure the information provided to participants is standardized, the following procedures will be adopted:

Standard operating procedures: all the initial information given to explain the study will be saved in a document to be forwarded to the interested mothers. A flowchart of interventions with topics to be followed will be provided to ensure that investigators always address the same subjects.

Observed home visits: research staff will randomly be chosen to be accompanied by other investigators during some visits, to check for adherence to operating procedures.

Training: periodically, researchers will be trained to apply food recalls, anthropometric measurements, and questionnaires.

Data collection: 10% of the sample will be subject to a quality call to ascertain whether the interventions are being conducted as proposed. These preliminary results will be communicated to all researchers responsible for the interventions, in order to assess the needing to optimize the information-oriented interventions. If there is a need for improvement, this sample will receive reinforcement information regarding the complementary feeding method.

Data audits: Inter-evaluator TEM which consists of repeated anthropometric measurements, will be calculated annually on a sample of 10 participants by the research staff who are responsible for obtaining anthropometric measurements.

If any modification in the study protocol is necessary, a notice will be sent to the Ethics Committee of the HCPA and the Universidade Federal do Rio Grande do Sul (UFRGS), the ReBEC, as well as the researchers and the participant families.

The researchers will carry out preliminary analyzes throughout the study period, informing the responsible professors about its progress. The professors will make the final decision to complete the trial, after the inclusion of all participants, according to the sample calculation. When applicable, study updates will be added to the Brazilian Clinical Trials Registry (REBeC). Any situation unexpected by the survey will be evaluated individually. All professors and researchers will be notified and, if necessary, the family will be referred to their health professional or pediatrician.

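### Harms outside the listed outcomes are monitored only if attributed to the trial, and notices of unexpected situations do not except the blinded assessors

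*Protocol article*

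**What the plan says.** The Adverse events section opens with the scope of safety monitoring: "We intend to monitor any adverse event caused by the trial participation". It then names two harms that come from routine data collection: "Presence of choking incidents will be identified in the questionnaires along with possible growth faltering", the latter from the 9- and 12-month anthropometry. It closes by promising attention to repeated events in one child and to events that are frequent across children.

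The Choking section gives the instrument for the first of these: "At the 9-month and 12-month visits, choking and gagging will be assessed by specific questions regarding frequency".

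The Quality control section says that situations the study did not foresee are assessed case by case, and continues: "All professors and researchers will be notified and, if necessary, the family will be referred to their health professional or pediatrician".

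On blinding, the Randomization section says: "Assessment data will be collected by a different researcher from the one responsible for the intervention, blinded to the allocation group, in a different room". The 9-month home visit (Study groups) is made by two blinded researchers, with anthropometry done before the questionnaire, "as some answers given might reveal the allocation group". Anthropometric measures again requires blinded measurers.

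**The concern.** Two stated rules pull against the between-arm comparison.

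First, causal attribution comes before recording rather than after it. This is an open-label behavioural trial: mothers learn the arm at the first intervention, and the staff who teach the allocated method know it too. Whether an event was due to taking part is therefore a judgement that someone aware of the arm may make. The Background says that "the conventional method, Parent-Led Weaning (PLW), is still advised, and there are no recommendations for a baby-guided approach in Brazil", so an event under PLW may look like ordinary weaning, while the same event under BLISS or the mixed method may look like a product of the trial. The Study design section, however, expects BLISS and the mixed method to be superior, which could discourage attribution in those arms. Either way the recorded set of events may depend on the arm, and no later analysis can recover an event that was never recorded.

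Second, an account of an unexpected feeding situation may mention the form of the food or who fed the child. If it goes to every researcher, it can reach someone who still has to measure that child blind, including for the primary anthropometric outcome.

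**Working it through.** The documents give no figure for this point, so the check is mainly a comparison of sections.

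**Step 1. What escapes the causal condition.** These are collected in every arm with no causal test:
- choking and gagging, by specific questions at 9 and 12 months (Choking);
- growth faltering, from measured anthropometry (Adverse events, Anthropometric measures);
- eating difficulties, by the MCH-FS (Questionnaires);
- functional constipation, through the 12-month questions on intestinal habits (Outcome measures, Questionnaires);
- iron status, by blood test at 12 months (Biochemical assessment);
- caries, gingival status and dental development (Oral health evaluation).

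**Step 2. What remains.** Harms not on that list, for example aspiration (which the Background names as a consequence of feeding difficulties), hospital visits, food reactions and unanticipated events. For these the article describes no unconditional collection. The only rule that covers them is the opening sentence of Adverse events, and it carries the causal condition.

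**Step 3. Who may judge cause.** The sources of such reports are mothers, who know the arm from the 5.5-month workshop (Randomization, Study groups), and staff. Between visits every mother has a dietitian's personal number (Study groups), so a report may first reach someone who knows the arm.

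**Step 4. Notices against blinding.** Randomization, Study groups and Anthropometric measures all require blinded assessors. Study groups accepts that answers about feeding can give the arm away and orders the 9-month visit accordingly. Quality control then sends notice of unexpected situations to all researchers and makes no exception. The same section does restrict recipients elsewhere: results of the 10% quality call go to the researchers responsible for the interventions. A limited recipient list is therefore already in use.

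**Step 5. Illustration; every rate is assumed.** Let p be the true event risk, equal in two arms of 48 (the arm size is from Sample size), and let a₁ and a₂ be the probabilities that an event is attributed to the trial.

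Expected recorded events = 48 × p × a; apparent risk ratio = (p × a₁)/(p × a₂) = a₁/a₂, whatever p is.

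With p = 0.20 and a₁ = 0.90, the first arm has 48 × 0.20 × 0.90 = 8.6 recorded events. The other arm has:

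| a₂ | Recorded events | Apparent ratio |
|---|---|---|
| 0.90 | 8.6 | 1.00 |
| 0.70 | 6.7 | 1.29 |
| 0.50 | 4.8 | 1.80 |
| 0.30 | 2.9 | 3.00 |

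If the attribution runs the other way, the ratios invert (for example 0.30/0.90 = 0.33). The table shows how the mechanism works. It is not evidence of how large the effect is in this trial, because the output only restates the assumed attribution rates.

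**The case against.** The best defence has five parts.

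- *The harms that matter most are collected systematically.* This stands. A reader might infer from the opening sentence of Adverse events that every harm is kept only if judged causal. The listed outcomes show otherwise, and the point is confined to the residual events in Step 2.
- *The text describes no adjudication or discard rule, and the section's last sentence speaks of adverse events without the causal qualifier.* This stands in part. No discarding is stated. But that last sentence can equally be read as referring to events already within the stated scope, and nothing else in the article widens that scope.
- *No between-arm tally of residual events is planned.* This stands. Neither Outcome measures nor Statistical analysis lists one, so the documents do not support saying that a planned comparison of harms is invalid. The promised watch for events that are common across participants still depends on the events being recorded.
- *The notification sentence is not about adverse events and does not say that the arm is disclosed.* This stands. It concerns unexpected situations, participants carry code numbers, and choking and growth faltering are anticipated. A reader might infer that assessors will be unblinded; the text supports only a possibility, because an account of feeding may reveal the method.
- *This is a condensed article, and causality procedures and the content of notices may sit in operating procedures not shown.* This stands as far as omissions go: the lack of a named judge is not held against the protocol. The causal condition and the recipient list, however, are stated rules and can be reviewed as written.

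**Conclusion.** The point holds in limited form. For harms outside the systematically collected outcomes, monitoring is conditional on attribution to the trial, in a design where those who report and handle events may know the arm. Recording may therefore differ by arm. The direction is unknown: the documents give a reason for over-attribution in the new methods and a reason for under-attribution, so it would be wrong to infer that BLISS or mixed harms will be overcounted. The size is also unknown, because no event or attribution rate is given.

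Separately, the notification rule sits badly with the protocol's own assessor blinding. It opens a possible route to unblinding; it does not establish that unblinding will occur.

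Both conclusions rest on reading the two sentences as they stand and on the assumption that no document not shown already widens the recording or restricts the notices. Neither affects the choking questions or the other listed outcomes through the causal condition. This is an inexpensive improvement in wording, not a demonstrated bias.

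**What to change.** (a) In Adverse events, drop the causal condition from the scope. State that all adverse events are recorded in all three arms with the same questions whatever their cause, and that causality is entered afterwards in a separate field, preferably by someone unaware of the arm.

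(b) In Quality control, limit notices of unexpected situations to the responsible professors and the intervention staff. Alternatively, remove anything that could reveal the arm before a notice reaches researchers who still have outcome measurements to take. Leave the referral of families as it is.

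The cost is two sentences of protocol wording and one item on existing questionnaires. The downside is a longer list of minor, unrelated events.

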### Saliva collection and DNA extraction

Total DNA will be extracted from samples of oral mucosal cells present in saliva, collected with a sterile swab. The samples will be stored at − 20 °C in their collection tubes until processing. DNA extraction will be performed with a QIAamp DNA Mini Kit, which produces samples with high purity and yield. Quantification will be performed in an L-Quant system (Loccus).

### Analysis of polymorphisms

Nine SNPs previously associated with feeding preferences will be analyzed: rs1726866, rs713598, and rs10246939, located in the candidate gene *TAS2R38*; rs1376251, located on *TAS2R50*; rs846672, located at *TAS2R16*; rs35874116 and rs9701796, located on *TAS1R2*; and rs307355 and rs35744813, located in *TAS1R3*. Real-time PCR analysis will be used to determine the genotypes and polymorphisms through TaqMan® SNP genotyping assays, using the QuantStudio 3 Real-Time PCR System.

### Flavor acceptance test

The test will be performed as proposed by Schwartz, Issanchou, and Nicklaus (2009). Children will be offered solutions tasting of each of the predominant basic flavors: sweet, salty, sour, bitter, and umami [70]. The solutions will consist of mineral water and flavorings whose molecules can be easily found in the amniotic fluid during pregnancy, in breast milk, infant formula, or in complementary foods: lactose for sweet taste, sodium chloride for salty taste, urea for bitter taste, citric acid for sour taste, and monosodium glutamate for umami flavor.

Concentrations will be titrated to generate moderate flavor intensity by diluting 3.42 g of lactose, 0.25 g of sodium chloride, 0.057 g citric acid, or 0.085 g monosodium glutamate in 50 mL of mineral water (0.16 g urea will be diluted in 15 mL of water). Parents will be instructed to offer milk or water to the child 1 h before the test, and no more food or drink thereafter, to limit the variability of thirst and hunger and its potential impact on the acceptance of different flavors. The solutions will be offered in a container to which the child is accustomed (bottle or glass), as follows: one solution will be offered for 45 s, followed by a 15-s break; another 45-s offer of solution, another 15-s pause; an offer of water, followed by a 1- to 2-min pause before the next solution is offered. The test will be filmed for later analysis on a hedonic scale.

The solutions will be offered by a blinded researcher and weighed before and after the test. Flavor acceptance will be evaluated two ways: calculation of ingested volume and hedonic scale. The latter will be based on the child's facial and body reactions, on a scale of 5 points: (1) strong rejection, (3) mild rejection, (3) neutral reaction, (4) mild acceptance, and (5) strong acceptance.

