### Oral health evaluation

At the 12-month visit, the visible biofilm and gingival bleeding will be recorded for each tooth surface [71]. With a clean dental surface after professional toothbrushing, the dental caries assessment will be performed using the International Caries Detection and Assessment System to detect Early Childrenhood Caries [72].

Primary dentition development and occlusal pattern will be determined by two previously calibrated examiners and the following variables evaluated: presence or absence of deep overbite, open bite, anterior crossbite, posterior cross bite, and overjet [73].

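### Flavor acceptance test: the hedonic key uses code 3 twice, ingested volume has no stated water reference, and the test's place in the 12-month visit is not fixed

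*Protocol article*

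**What the plan says.** All of this is in the Protocol article. The abstract lists acceptance of bitter and sweet flavors among the secondary outcomes. The Flavor acceptance test section sets two measures: "Flavor acceptance will be evaluated two ways: calculation of ingested volume and hedonic scale".

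- **Volume.** "The solutions will be offered by a blinded researcher and weighed before and after the test". On the container: "The solutions will be offered in a container to which the child is accustomed (bottle or glass"). Each solution is presented twice for 45 s, with 15-s breaks. Water follows, for a time that is not given, and then a pause of 1 to 2 minutes. Weighing is mentioned for the solutions only.
- **Thirst.** "Parents will be instructed to offer milk or water to the child 1 h before the test, and no more food or drink thereafter", with the stated aim "to limit the variability of thirst and hunger and its potential impact on the acceptance of different flavors".
- **Hedonic score.** It is rated from filmed reactions on what is called a 5-point scale, with the key ("1) strong rejection, (3) mild rejection, (3) neutral reaction, (4) mild acceptance, and (5) strong acceptance".
- **Visit content.** For the 12-month visit, the Study groups section (text after Table 1) names the blood draw first. Later it says "an intraoral examination will be performed, and the end-of-study questionnaires will be administered, as well as a flavor preference test". The Oral health evaluation section adds toothbrushing to the dental assessment: "With a clean dental surface after professional toothbrushing".

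**The concern.** The two measures are exposed to different errors, so one does not make up for the other.

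Volume is a weight difference. It reflects how much a child drinks in general, how fast the container delivers in a fixed 45 s, and anything spilled, as well as liking. No reference intake for the same child is stated, although plain water is offered in the same session.

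The hedonic score does not depend on the amount drunk, but it is read from the child's reactions. A child recently upset by a needle or an oral examination may look as if it rejects whatever is offered. The printed key also cannot separate mild rejection from neutral.

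At stake are the arm comparison for this secondary outcome and the link to taste-receptor genotype, which the Food preferences background motivates and for which nine SNPs are typed. Extra variance or merged categories would mainly hide real differences.

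**Working it through.** The plan gives no figure for this outcome, so there is nothing to reproduce. The check compares the texts and uses arithmetic with assumed inputs.

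**1. The key.** Five ordered labels carry the codes 1, 3, 3, 4, 5, which are four distinct values. Let q be the share of responses that are mild rejection. Against a 1-to-5 key,

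mean as printed = intended mean + q × (3 − 2) = intended mean + q.

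A difference between two arms is shifted by q₁ − q₂. A move from neutral to mild rejection registers as 0 instead of 1 point.

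**2. Dilution of volume.** Assume 48 per arm (the plan's group size), a true taste difference of 0.5 SD, a two-sided 5% level, and a share r of the volume variance unrelated to taste. The documents do not give r. Then d = 0.5 × √(1 − r), and power ≈ Φ(d × √(48/2) − 1.96).

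| r | d (SD) | power |
|---|---|---|
| 0 | 0.50 | 69% |
| 0.25 | 0.43 | 56% |
| 0.50 | 0.35 | 41% |
| 0.75 | 0.25 | 23% |

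**3. Container and arm.** If a glass adds c mL per solution relative to a bottle, and glass use is p₁ and p₂ in two arms, the spurious difference is (p₁ − p₂) × c. It is 0 if use is equal. With assumed use of 60% and 30% and c of 3 to 5 mL, it is 0.30 × 3 = 0.9 mL to 0.30 × 5 = 1.5 mL. None of these inputs is in the documents.

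**4. What a water ratio can and cannot do.** Assume a true intake of 5 mL solution and 10 mL water.

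- Bottle: 5/(5 + 10) = 0.33.
- Container or thirst multiplies both by k: 5k/(5k + 10k) = 0.33. The effect cancels.
- Glass adds 4 mL of spillage to each: 9/(9 + 14) = 9/23 = 0.39. The effect does not cancel.

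The ratio therefore removes proportional differences but leaves additive spillage, which is why spillage has to be recorded separately. Water also follows each solution, so its intake may depend on the taste just given.

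**5. Order.** The Study groups text puts the blood draw at the start of its list and the flavor test towards the end, after the intraoral examination, but uses no words of sequence within the visit. Toothbrushing appears only in the Oral health evaluation section, which follows the flavor test section. No passage puts the flavor test before either procedure, and none puts it after.

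**The case against.** The strongest reply is that little here is stated wrongly.

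- **Thirst.** A reader might infer that thirst is uncontrolled. It is not: the one-hour rule is there for that purpose, and a pause separates the solutions. This stands. What remains is that the child may have milk or water, in any amount.
- **Order.** A reader might infer that the test is scheduled after venipuncture and toothbrushing. The documents do not say so; the list is an inventory. This stands, and distress is a risk, not a planned feature. It would also be expected in all arms, so it acts mainly as noise.
- **Arm bias through the container.** A reader might infer that self-feeding arms use a glass more often. The group descriptions differ in food consistency and adult participation, with no arm-specific advice on cup or bottle. Container habit at 12 months does arise after allocation, so randomization does not guarantee balance, but a difference is only assumed.
- **Indexing left to other sources.** The cited published procedure or an analysis plan, neither shown, may define an index. That is possible. The article itself names volume and the weighing of solutions only.
- **Within-child contrasts already exist.** Five tastes per child allow sweet against bitter. This stands in part. The bitter solution is prepared in 15 mL and the others in 50 mL, so if those are the amounts offered, the ceilings differ.
- **The code is a misprint.** Very likely, since five labels and 5 points are named. It is still the scoring key and should be corrected.

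**Conclusion.** The point holds as a modest measurement issue in one secondary outcome. The key is wrong as printed and leaves four codes for five categories. Volume, as described, mixes taste with general intake, container flow and spillage, and the one-hour rule reduces only the thirst part. The place of the flavor test in the visit is open, which leaves the reaction-based score exposed to distress.

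The likely effect is loss of sensitivity. Its size depends on the unknown share of non-taste variance: between a quarter and three quarters, power in the illustration runs from 56% down to 23%, against 69% with none. The documents do not support a claim that the arms will be biased, that the test follows the needle, or that a ratio to water cures the volume measure. The primary growth outcome is unaffected.

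**What to change.** 1. Give mild rejection code 2 in the key and on the scoring sheet.
2. State that at the 12-month visit the flavor test comes before venipuncture and before the oral examination with toothbrushing.
3. Weigh the water already offered after each solution, and give it a fixed offer time.
4. Report solution/(solution + water) within child for each taste alongside volume, not in its place. State its limits: additive spillage remains, and water intake may carry over from the preceding taste.
5. Record container type and visible spillage for each child, so that both can be described by arm and used in a sensitivity analysis.

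The cost is a few extra weighings, two more fields on the form and a slightly later blood draw. Children already tested cannot be indexed afterwards if their water was not weighed. Their hedonic scores can be recoded from the film.
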